#### **Criteria for stopping the study**

1. The Principal investigator will closely monitor and analyse study data as it becomes available and will make determinations regarding the presence and severity of the adverse events
2. Any grade 3 systemic event assessed by DSMB as possibly, probably or definitely related to the vaccination (following exclusion of other unrelated common causes) or if one volunteer experiences grade 4 or 5 (death) SAE assessed as possibly, related to the vaccination.

The study injections and enrolments would resume only after review of the adverse events by the DSMB and a decision by the TCC including the Chairman resulted in a recommendation to permit further study injections and study enrolments. Safety data and changes in study status will be submitted to the ethics committee.

### **CLINICAL MANAGEMENT**

The clinical trial team who will assess and treat the event as appropriate will manage events.

#### **Management of HIV issues during and following the trial**

Individuals who test HIV-positive during the screening process will be referred for HIV care, treatment and support at the HIV/AIDS clinic MNH. At this clinic the following services will be provided; sustained counseling about HIV/AIDS, counselling on diet, management of symptoms and opportunistic infections as well as provision of antiretroviral drugs if indicated

#### **HIV testing**

Only volunteers with a non-reactive antigen/antibody HIV ELISA result will be enrolled. A risk assessment will be undertaken prior to every immunisation and if risk status has changed then immunization may have to be delayed until the HIV status of the volunteer is clarified.

It is possible that volunteers may develop antibodies and test 'positive' in routine commercial HIV ELISA assays subsequent to immunisation. The laboratories at MUHAS, department of

Microbiology/Immunology, will conduct molecular tests (HIV-1 DNA PCR) to distinguish between infection and a post-immunisation response required either for clinical management, or at the request of a volunteer.

Weeks 40, 60, 76 and 104 specimens will be tested in real-time by antigen antibody ELISA and DNA PCR if found to be ELISA positive, so that volunteers can be informed of the result before the end of the trial and a plan to recall and retest them made should this be necessary. In the event of ongoing post-immunisation positive ELISA, the volunteers will be invited to re-attend specified centre annually until such time as this response has disappeared, and provided with an explanatory identity card in the interim.

#### **Verification of HIV status of volunteers**

If certification is required at the request of the recruited volunteer, this can be provided by the trial Principal investigator after testing at the trial laboratory. Results will always be given at post-test counseling session by a member of the study team, unless the volunteer requests otherwise. If a specimen from a volunteer suggests that the volunteer is HIV infected, a second specimen will be collected, retested and the results confirmed. If a volunteer for any reason needs to establish his or her HIV status extended tests will be offered as described above.

#### **Management of volunteers who acquire HIV infection during the study period**

In the unexpected circumstances that a volunteer in the trial acquires HIV infection they will be managed in the following way:

##### *Referral for clinical care*

Volunteers will be referred initially to a study HIV specialist physician at MUHAS/MNH for a full discussion of the clinical aspects of HIV infection and planning for further care. Further investigations will be undertaken as necessary. At this clinic the following services will be provided, sustained counseling about HIV/AIDS, counselling on diet, management of symptoms and opportunistic infections as well as provision of antiretroviral drugs if indicated. Efforts will be done in collaboration with the Ministry of Health that such individuals are assured of life-long follow up at MNH/MUHAS in terms of their immunological and clinical fate

##### *Referral for counseling*

A referral to a counselor at the HIV clinic at MNH will be arranged by the specialist physician. The counseling process will assist the volunteer in the following issues:

- a. Psychological and social implications of HIV infection
- b. Who to inform and what to say
- c. Implications for sexual partners
- d. Facilitation of risk reduction plan
- e. Avoidance of risk to others in the future
- f. Information on available medical treatment

##### *Informing the other involved health care personnel*

The volunteer will be encouraged to do this, but the decision will remain at the discretion of the individual.

##### *Immunological follow-up*

Follow-up of HIV infected individuals who have received study vaccine products will be determined by the Trial Management Group for the duration of the study and after the study period they will be referred to the existing treatment center. The intensity of assessments will be dependent on clinical progression, including changes in surrogate markers such as CD4 count.

If a volunteer is found to be HIV-infected during the trial, he/she will be excluded from further immunizations in the trial.

#### **SOCIAL DISCRIMINATION AS A RESULT OF A POST-VACCINE RESPONSE**

The aim is to minimize the possibility of social discrimination in volunteers who develop a positive HIV-ELISA test by providing HIV testing by PCR and certification for volunteers as required. In addition, an identification card stating that the individual has participated in a vaccine trial, with a contact number in case of medical emergency, will be provided. In the unlikely event that a volunteer suffers social discrimination as a result of a post-vaccination response, the clinical investigators will assist the volunteer.

## **TRIAL DATA MANAGEMENT**

### **Data management at the Clinical Centre**

Data will be recorded directly onto the case report forms, which will provide the majority of source data for the trial. There will be some additional source data in the clinical notes, such as medical history related to eligibility, results of laboratory analyses, dates of visits including immunisation, and details of clinical management (description of adverse events and concomitant medication). The Clinical co-ordinator or his/her designate will cross-check the completeness of the CRF's at the clinic. The original copy will be kept at the clinic, and one photocopy of the completed case report form will be forwarded to the trial external monitor at the Karolinska Institute, Sweden for inspection by the monitor and entry into the database. Another data base will be maintained at the HIVIS office, Makuti, MNH. Any changes to the CRFs should be signed and dated, including changes made before a copy is forwarded to the trial monitor and data entry. Study related documents including clinical notes and original laboratory results should be kept in a secure location at MUHAS after completion of the trial.

### **Data management in the Microbiology/Immunology laboratories**

Standardised operating procedures will be followed in all laboratories to ensure the quality of data. Data will be stored in both hard copies and electronically in an agreed format and data files transferred to trial coordinating centre for the main analysis. As for clinical data all results from the laboratory will be reviewed by the laboratory investigator for completeness before forwarding them to the trial coordination centre database. He/She will review both the electronic forms and hard copies and approve them by signing the copies. The original copy will be stored at the laboratory and one copy sent to the trial coordination center for data entry.

### **Data management at the trial coordination centre (Karolinska Institute)**

All CRFs will be reviewed for completeness and inconsistencies by the data manager according to standardised operating procedures. Any enquires will be communicated with the clinical centre and will be passed for review by the trial physician if required. The data manager will approve the CRFs for data entry into the database. Data will be coded and doubly entered into a computerized database. Consistency checks and range checks will be performed at the data entry level.

After approval and entry into the database, the copy including documentation detailing all the queries and changes will be stored in a study specific binder at the trial coordination centre. The documents in the binder will be organized according to study number. The original case report forms will be stored together with the individual source data at the clinical centre.

### **Archiving**

Study related documents including clinical notes, completed CRFs and original laboratory results, hard copies and electronic copies will be kept in a secure location at MUHAS.

## **STUDY MONITORING**

A trial monitor will be appointed by the sponsors of the study, MUHAS and SMI; he/she will be responsible to the Principal Investigators of the Project and the Trial Coordinating Committee to ensure that the trial is conducted according to ICH GCP guidelines including monitoring vaccine data consistency, vaccine accountability, dispatch and arrival of immunological specimens.

### *Preparation of reports to assist the monitoring*

The monitor will visit the clinical centre to validate trial data against the clinical records. The following data should be verifiable from source documents: (Initials, study registration number, sex, birth date, address)

- i. Documentation of any existing conditions or past conditions relevant to eligibility
- ii. A ☐ signed consent
- iii. Dates of visits including dates of immunizations
- iv. Source verification of all data entered into the database
- v. Grade 3 or 4 adverse events and any events leading to discontinuation of the immunisation schedule
- vi. Concomitant prescribed medication

Vaccine stocks will also be monitored at visits to the clinical centre/pharmacy.

## **DATA OWNERSHIP**

The data generated in this study will be the property of the HIVIS Investigators and will be held on their behalf by MUHAS until completion of the study or until it is stopped. Thereafter the data will be passed over to MUHAS for archival purposes according to accepted regulation for a maximum of 5 years. If required at an earlier date for the purposes of regulatory submissions, a request should be made to the Trial Coordinating Committee.

## **TRIAL COMMITTEES**

### **Trial Coordinating Committee (TCC)**

The supervision of the trial will be a responsibility of the Trial Coordinating Committee (TCC). The committee will have an independent chair and a secretary. The members will include the 2 Principal Investigators, study director, clinical co-ordinator, laboratory co-ordinator, study nurse and data manager. The TCC will be meeting at least once a week during the trial period. The TCC will prepare a monthly report for presentation at the HIVIS governing board meeting. This committee will be responsible for final decisions about grade of adverse events and relationship to study vaccine. Notes of meetings will be kept, and the Committee will report to the HIVIS Project Governing Board. The trial may be terminated by this Committee for any reason, including on the recommendation of the DSMB.

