### **Reporting adverse events**

Adverse events should be recorded on the appropriate case record form (CRF 8-III). Any grade 3 or 4 adverse event (see *appendix xiv*) or any event resulting in discontinuation of the vaccination schedule should be reported within 2 working days to the DSMB for review and appropriate recommendations. The proposal as to whether continue or discontinue the study will be submitted to the monitor, TCC, NIMR and TFDA for further review and action

**Serious adverse events** should be reported to the monitor the same working day that the Clinical Investigator becomes aware of the event fulfilling the above criteria. This can be done by telephone, e-mail or fax. The minimum criteria required in reporting a SAE are the volunteer identifiers (trial number/ date of birth/initials), reporting source (name of Investigator), and why the adverse event is identifiable as serious. The adverse event reporting telephone/ fax number for MUHAS is [name] (HIVIS office). The address for reporting to the monitor will be determined by the study monitor.

The monitor will confirm that the event is potentially reportable and arrange for urgent review of the case by the TCC within 2 working days. Should the case be considered reportable by this group, a report will be prepared by the clinical investigator or his deputy and filed with the TFDA and the DSMB. The Principal Clinical Investigator is responsible for notifying the Local Research Ethics Committee.

Examples of SAEs that do not require expedited reporting include:

1. Hospitalisation for scheduled surgery unrelated to vaccine, other than temporally (within 30 days).
2. Orthopaedic or traumatic injuries requiring hospitalization.
3. Hospitalisation planned for pre-existing conditions not due to an aggravation in the condition.
4. SAEs occurring more than 30 days after vaccination or having appeared before vaccination without any aggravation after vaccination

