### **Data and Safety Monitoring Board (DSMB)**

An independent Data and Safety Monitoring Board will be appointed by the sponsor of the study, MUHAS and SMI. The role of the DSMB will include;

1. To review the research design and the plans for data and safety monitoring
2. To receive and review at intervals the progress reports from the investigators
3. To monitor safety data
4. To monitor and evaluate trial progress, including
  - a. Periodic assessment of data quality and timelines
  - b. Performance of the study sites
5. To recommend to the sponsor, local IRBs and investigator concerning continuation or to stop the study.

The DSMB will meet whenever a safety report has been submitted and make a recommendation to the TCC within 7 days as to the future conduct of the trial.

They will also meet on one occasion to review the safety data, after half the volunteers have received the first immunization in order to make recommendations to the sponsors of the study.

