#### *Analysis*

All safety end-points will be graded by the Clinical Investigator and reviewed by the Trial Management Group. Any queries about grade and relationship to study product that cannot be resolved will be referred to the Trial Coordinating Committee for a final decision.

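### The grade 3 stopping rule depends on the DSMB's relatedness assessment while the TCC holds final say on grade and relatedness; neither is ranked above the other, and no mandatory hold applies while the DSMB assesses

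*Protocol*

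**What the plan says.** Under Criteria for stopping the study, the first limb of the rule is "Any grade 3 systemic event assessed by DSMB as possibly, probably or definitely related to the vaccination (following exclusion of other unrelated common causes". The same sentence goes on, "or if one volunteer experiences grade 4 or 5 (death) SAE assessed as possibly, related to the vaccination". The first limb names the DSMB as assessor; the second names nobody explicitly. After a stop, injections and enrolment resume only following DSMB review and a TCC decision.

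The Trial Coordinating Committee section says: "This committee will be responsible for final decisions about grade of adverse events and relationship to study vaccine". It makes no exception for events that fall under the stopping rule. The listed members are the two Principal Investigators, the study director, the clinical and laboratory co-ordinators, a study nurse and the data manager, with an independent chair and a secretary. The Analysis section adds: "Any queries about grade and relationship to study product that cannot be resolved will be referred to the Trial Coordinating Committee for a final decision". It does not mention the DSMB.

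On timing, Reporting adverse events requires that any grade 3 or 4 event, or "any event resulting in discontinuation of the vaccination schedule should be reported within 2 working days to the DSMB". The DSMB section then says: "The DSMB will meet whenever a safety report has been submitted and make a recommendation to the TCC within 7 days".

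**The concern.** Grade and relatedness are the two inputs to the stopping trigger. One section gives the relatedness input to the independent board; another gives the final word on both inputs to the committee that runs the trial. If the two bodies differ on whether a grade 3 systemic event is possibly related, the protocol does not say whose view decides whether the trial stops.

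The second difficulty is timing. For grade 3, the trigger is the DSMB's finished assessment, so the rule cannot act while the assessment is under way. A rule that halts the trial on a single related grade 3 systemic event treats such an event as serious enough to pause for. As written, other volunteers may still be injected until the board has reported, unless someone uses a discretionary power.

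**Working it through.** **Who decides.** The relevant sections, side by side:

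- Criteria for stopping the study: the DSMB assesses relatedness for grade 3. The assessor for grades 4 and 5 is not explicitly named.
- Trial Coordinating Committee: the TCC makes final decisions on grade and relationship, without exception.
- Analysis: queries on safety end-points left unresolved after investigator grading and Trial Management Group review go to the TCC.
- Data and Safety Monitoring Board: the board is independent and makes recommendations on continuing or stopping.

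None says that the DSMB's assessment binds the TCC for the stopping rule, or the reverse.

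**What could stop injections before the DSMB has assessed a grade 3 systemic event.**

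- Discontinuation procedures: the clinical investigator may withhold the affected volunteer's next injection. This is discretionary and concerns one person.
- Criteria for withdrawal, item 3: mandatory, but only for the affected volunteer and only once the event is classified as probably or definitely associated.
- Criteria for withdrawal, items 8 and 9: the sponsor, vaccine provider, principal investigator or an ethics committee may stop the study. Discretionary.
- Trial Coordinating Committee: may terminate for any reason. Discretionary.
- Indications for additional review: an extra meeting after three or more volunteers; no hold.

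No mandatory trial-wide hold appears in the list.

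**Length of the window** (assuming both limits are used in full and run one after the other).

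- Reporting: 2 working days is 2 calendar days (Monday to Wednesday) or 4 (Thursday to Monday).
- Recommendation: up to 7 days.
- Total: 2 + 7 = 9 days, or 4 + 7 = 11 days.

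**Exposure in the window.** Enrolment is complete in this version, so what remains at risk is mainly the boosts. On 19 May 2008, 26 of 60 volunteers had received the first MVA/placebo injection, so at most (60 − 26) + 60 = 94 MVA/placebo injections were still to come. There would be fewer if volunteers declined the new consent or were withdrawn.

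The protocol gives no boost rate, so the enrolment pace is borrowed as an assumption: 60 volunteers from 20 February 2007 to 26 February 2008, which is 371 days.

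- Injected in 9 days: 60/371 × 9 = 1.46. In 11 days: 60/371 × 11 = 1.78.
- Active share 40/60: 0.97 to 1.19 active doses.

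As a sensitivity check, suppose boosts ran at 3 per week, the cap that the protocol set for early enrolment. Then 3 × 9/7 = 3.9 to 3 × 11/7 = 4.7 volunteers would be injected, or 2.6 to 3.1 active doses. Delayed MVA supply could bunch the second boosts, so the enrolment pace is not an upper bound.

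**The case against.** The strongest reply is that the sections can be read together. The stopping criteria are the specific rule and name their own assessor; the TCC paragraph is a general description of a committee, and the Analysis sentence concerns grading of end-points. On ordinary construction the specific rule governs. This has real force, and it is why the wording favours the DSMB. It does not remove the need for a sentence saying so, because the TCC's authority is called final and covers exactly the same two judgements. The missing assessor for grades 4 and 5 may likewise be mere ellipsis, carried over from the start of the sentence; the text allows that reading but does not fix it.

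A reader might infer that the TCC could quietly overrule the board. The documents do not support that. The DSMB's role includes advising the sponsor, local IRBs and investigator as well as the TCC. The proposal to continue or discontinue also goes to the monitor, NIMR and TFDA, and NIMR or the MUHAS ethics committee can stop the study. A disagreement would be visible.

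On the hold, the requirement of DSMB review before resumption hints at a pause during review, but it presupposes that a stop has already happened. It is fair to add that a grade 3 event that is also serious goes to the monitor the same working day and to TCC review within 2 working days, and that the TCC meets at least weekly. A discretionary stop could therefore come quickly.

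A reader might also infer that a death after the last injection would never reach the DSMB, since the direct route names grades 3 and 4 and, for serious events, the TCC acts first: "Should the case be considered reportable by this group, a report will be prepared by the clinical investigator or his deputy". That goes too far. The DSMB receives progress reports and monitors safety data independently of that route, and ethics committees are informed of serious events. The item "SAEs occurring more than 30 days after vaccination or having appeared before vaccination without any aggravation after vaccination" is an example of what needs no expedited report, not an exemption from reporting. What stands is a small inconsistency: death is grade 5 and is part of the stopping trigger, yet grade 5 is absent from the list of grades sent directly to the board.

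**Conclusion.** The point holds in limited form and should be fixed. Two defects are in the text itself: authority over the stopping trigger's inputs is given to two bodies without a ranking, and no mandatory hold covers the up to 9 to 11 days before the grade 3 trigger can be met. The practical size is modest: roughly one active dose per event at the enrolment pace, and about three at the faster illustrative rate. These figures assume that both time limits are used in full and consecutively, and that the boost rate resembles one of the two rates used. The protocol gives no count of grade 3 systemic events, so the number of such windows cannot be estimated. The case for changing the text rests on the clarity of the trial's main safety rule, not on a large expected exposure.

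**What to change.** In Criteria for stopping the study and in the Trial Coordinating Committee section, state that for the stopping rule the DSMB's assessment of grade and relatedness is decisive for grades 3 to 5, and that the TCC's final say there and in Analysis applies to other grading queries.

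In Criteria for stopping the study, add a hold: once the investigator judges a grade 3 systemic event, or a grade 4 or 5 serious adverse event, at least possibly related after common causes such as malaria have been excluded, no further injections are given until the DSMB has assessed it.

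As a minor consistency edit, extend the direct DSMB reporting list in Reporting adverse events from grades 3 and 4 to grades 3, 4 and 5.

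The cost is amendment wording, a few more DSMB reports, and occasional holds of up to 9 to 11 days that may move some boosts off their scheduled date. Excluding common causes first keeps the number of holds down.
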